## 10.2 Analysis methods

Analyses will be performed according to an intention-to-treat principle. All analyses will be adjusted for site of admission. All analyses will be adjusted for site of admission. The primary outcome and the first secondary outcome (complications) will be analysed using mixed effects logistic regression with site as a random intercept. RR will be estimated using the 'nlcom' STATA command or G-computation in R (R Core Team, Vienna, Austria). Count data (mechanical ventilation-free days) will be analysed by van Elteren test with site as a covariate. Secondary continuous outcomes (MoCA-BLIND and EQ-VAS) will be analysed using mixed effects linear regression with site as a random intercept.

All primary conclusions will be based on our primary outcome and, a priori, secondary and explorative outcome results will be considered as hypothesis generating. Based on this we will consider a P-value of 0.05 as a threshold for statistical significance for all analyses.

All primary conclusions will be based on our primary outcome and, a priori, secondary and explorative outcome results will be considered as hypothesis generating. Based on this we will consider a P-value of 0.05 as a threshold for statistical significance for all analyses.

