### 5. Trial design

The trial is a multicentre, randomized trial with a 1:1 concealed allocation. Participants will receive either protocolized restrictive administration of non-resuscitation fluids or usual care. The trial will be investigator-initiated and non-commercial. The steering group, author group, trial statistician, outcome assessors, prognosticators and the trial coordinating team will be blinded to group allocation. Please see Table 1 for a study schedule.

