### 10.1 Sample size

#### 10.1.1 Primary outcome

The sample size calculation is based on an expected 90-day mortality of 45 % in the control group (Hjortrup 2016, Perner 2012, Hernandez 2019, Holst 2014). To detect an absolute reduction in mortality of 7.5%, with an  $\alpha$  of 5% and a power of 90% the required sample size is 1808. We chose 7.5% as anticipated intervention effect because it is a realistic and clinically relevant effect size observed in previous large intensive care trials assessing interventions in critically ill patients (Perner 2012, Andersen-Ranberg 2023). To account for loss to follow-up and no-consent from some patients we will include a total of 1850 patients.

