### Background data

- Height (cm; Sites using imperial measurements: Record estimated height in feet and inches)
- Weight at baseline (kg, standardized according to local practice; Record the weight measurement taken closest to time of inclusion; Sites using imperial measurements: Record estimated weight in pounds (lbs))
- Body mass index BMI ( $\text{kg}/\text{cm}^2$ )
- Clinical Frailty Score (Patient's estimated level of fitness/frailty prior to hospital admission; Defined according to: <https://www.dal.ca/sites/gmr/our-tools/clinical-frailty-scale.html>)
- Baseline creatinine [lowest in the 12 months preceding randomization] ( $\mu\text{mol}/\text{L}$ )

- Charlson Comorbidity Index (Charlson et al. J Chronic Dis. 1987; 40: 373-83)
- Type of initial antimicrobial treatment
- Suspected pathogen (If culture was taken, indicate the culture result)
  - o Suspected pathogen sensitive to initial antibiotic treatment (sensitive/intermediate /resistant/not available)
- Hospital admission (dd-mmm-yyyy, hh:mm) (Date and time that the patient was admitted to hospital they were randomised at. If the patient was transferred from another hospital, record the date and time of admission to the hospital where the patient was randomised.)
- Hospital location prior to randomization a) Emergency department, b) Operating room, c) Other ICU, d) Other unit
- Steroid treatment prior to hospital admission (Y/N)
- Surgery prior to inclusion/randomization (Y/N), if yes, specify: a) Head and neck, b) Thorax, c) Abdominal/pelvic, d) Extremities, e) Trauma f) Other
- Origin of sepsis (Mellhammar et al. Crit Care Exp 2022; 4: e0697)

Baseline variables at study inclusion (values closest in time to enrolment, within  $\pm 6$  h, unless other timeframe is specified; lab values either arterial or venous.)

- Body temperature (degrees Celsius)
- SAPS-III (Simplified acute physiology score-III) (Moreno et al. Intensive Care Med. 2005;31:1345-55)
- Glasgow Coma Score (GCS) (Teasdale and Jennett B. Lancet. 1974; 2: 81-4)
- Creatinine ( $\mu\text{mol/L}$ )
- Renal replacement therapy (Y/N)
- Bilirubin ( $\mu\text{mol/L}$ )
- Platelet count ( $\times 10^9/\text{ml}$ )
- Mean arterial pressure (mmHg)
- Systolic pressure (mmHg)
- Type of inotropic drug or vasopressor (any dose of dobutamine, dopamine, vasopressin or other V1A agonists, levosimendan, angiotensin II, noradrenaline, adrenaline, milrinone, or other)

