- Noradrenaline dose (highest dose in the 6 hours prior to enrollment;  $\mu\text{g/kg/min}$ )
- Corticosteroid treatment (Y/N)
- Atrial fibrillation/flutter (Y/N)
- Ischemic events (Y/N) (criteria described above), if yes, specify: a) Limb, b) Cerebral, c) Heart, d) Intestine
- Heart rate (bpm)
- Ventilatory support (nasal catheter, nasal high flow oxygen, Hudson mask or similar, reservoir mask, non-invasive mechanical ventilation, invasive mechanical ventilation [defined as mechanical ventilation through an orotracheal tube or through a tracheostomy], none. Classification at each day will be based on the highest level of support,
- CRP (g/L)
- Leucocytes ( $\times 10^9$  cells/L)
- Haemoglobin (g/L)
- Potassium (mmol/L)

- Sodium (mmol/L)
- Chloride (mmol/L)
- Blood glucose (mmol/L)
- Arterial blood gas on inclusion (Y/N)
- FiO2 (%)
- PaO2 (kPa)
- PaCO2 (kPa)
- pH
- Base excess (BE, mEq/L)
- Volume of fluid intake in the 24h prior to inclusion (Crystalloids (Ringer's acetate/lactate [ml], 0.9% NaCl [ml], other [ml]); Colloids (Albumin 4-5% [ml], Albumin 20% [ml], other [ml]); Blood products (Erythrocytes [ml], Plasma [ml]- Platelets [ml]); Glucose (any concentration [ml]); Parenteral nutrition (ml); Enteral nutrition (ml); Enteral water (ml))

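### The primary model adjusts for site only; adding a few pre-randomisation covariates already planned for collection would raise power from 90% to perhaps 91-96% with no extra patients

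*Protocol*

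**What the plan says.** Section 10.2 fixes the primary method: "The primary outcome and the first secondary outcome (complications) will be analysed using mixed effects logistic regression with site as a random intercept". It states that all analyses are adjusted for site of admission and names no other adjustment variable. The risk ratio is to come from nlcom in Stata or G-computation in R. Section 5.1 stratifies randomisation by trial site only.

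Section 10.1.1 sets the size of the trial: "The sample size calculation is based on an expected 90-day mortality of 45 % in the control group", an absolute reduction of 7.5 points, and an alpha "of 5% and a power of 90% the required sample size is 1808". Recruitment is 1850, to cover loss to follow-up and refusal of consent.

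Appendix A lists several candidate covariates:

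- age and highest lactate, both recorded during screening;
- a Clinical Frailty Score, described as "Patient's estimated level of fitness/frailty prior to hospital admission";
- the Charlson Comorbidity Index;
- "Noradrenaline dose (highest dose in the 6 hours prior to enrollment";
- SAPS-III, under the baseline variables, which are the values closest to enrolment within plus or minus 6 h unless another timeframe is specified.

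Section 10.4 uses age, frailty and lactate as categorised subgroup variables. Section 10 announces a detailed statistical analysis plan before the last participant is randomised.

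**The concern.** In a trial with a binary outcome, adjusting for baseline variables that predict the outcome increases the power of the treatment test. Here neither the randomisation nor the primary model uses any patient-level prognostic information. Chance imbalance in, say, age or frailty is left in the primary comparison, and the precision that those variables could supply is not used. The data items are already planned, and G-computation already gives a route from an adjusted logistic model to a marginal risk ratio. The adjustment would therefore need no new patients and would leave the reported risk ratio with the same meaning.

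**Working it through.** **Inputs from the protocol.** Control risk 0.45; intervention risk 0.45 - 0.075 = 0.375; alpha 5%; power 90%; total 1808 (section 10.1.1). Allocation is 1:1 (section 5). The protocol does not state sidedness; two-sided is used because it reproduces the figure.

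**Step 1: reproduce the plan.** With pooled variance under the null, n per arm = [1.960 x sqrt(2 x p x (1 - p)) + 1.282 x sqrt(p1(1 - p1) + p2(1 - p2))]^2 / d^2, where p = 0.4125 is the mean risk and d = 0.075.

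- First term: 1.960 x sqrt(2 x 0.4125 x 0.5875) = 1.3645.
- Second term: 1.282 x sqrt(0.2475 + 0.234375) = 1.282 x 0.6942 = 0.8896.
- n = (1.3645 + 0.8896)^2 / 0.005625 = 903.3, rounded up to 904 per arm, or 1808 in all. This matches exactly.

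Power at 1808 is 90.0%, and 90.7% if all 1850 are analysed. A one-sided test would need only 1474.

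**Step 2: power with adjustment.** Let R2 be the share of outcome variance explained by the baseline covariates. To a good approximation, adjustment acts as if n per arm were 904 / (1 - R2). Power is Phi[(d x sqrt(n) - 1.3645) / 0.6942]. For R2 = 0.10, n = 1004.4 and the argument is 1.459, so power is 92.8%. The protocol gives no R2, so a range is shown.

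| Assumed R2 | Power at 1808 | Power at 1850 | Patients for 90% power, 1808 x (1 - R2) |
|---|---|---|---|
| 0 | 90.0% | 90.7% | 1808 |
| 0.05 | 91.4% | 92.0% | 1718 |
| 0.10 | 92.8% | 93.3% | 1627 |
| 0.15 | 94.0% | 94.5% | 1537 |
| 0.20 | 95.2% | 95.6% | 1446 |
| 0.25 | 96.3% | 96.6% | 1356 |

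**Step 3: simulation.** A logistic model with one standard-normal prognostic score was simulated, with marginal risks held at 45% and 37.5% and 4,000 trials per setting. Monte Carlo error is about sqrt(0.9 x 0.1 / 4000) = 0.5 points. At N = 1808:

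| AUC of score (assumed) | R2 | Unadjusted power | Adjusted power |
|---|---|---|---|
| 0.63 | 0.055 | 90.4% | 91.9% |
| 0.66 | 0.076 | 89.8% | 92.8% |
| 0.69 | 0.111 | 90.4% | 93.8% |
| 0.72 | 0.147 | 90.4% | 93.9% |
| 0.74 | 0.172 | 89.6% | 94.4% |
| 0.77 | 0.221 | 89.2% | 95.7% |

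The two methods agree closely. These runs leave site out. A further simulation with site in both models gave about 91-95% adjusted against about 90% site-only.

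**Step 4: effect on the estimates.** With the marginal risks held fixed, the odds ratio is 0.733 without covariates. Conditional on the score, it is 0.72 at AUC 0.63 and 0.69 at AUC 0.74. The marginal risk ratio stays at 0.375 / 0.45 = 0.83.

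**Step 5: which covariates are safe.** Section 5.2 starts the allocated fluid regimen within two hours of randomisation. A baseline value taken up to 6 h after enrolment can therefore postdate the start of treatment. Age, frailty before admission, Charlson index, screening lactate and noradrenaline dose in the 6 h before enrolment avoid this. SAPS-III, as now defined, does not.

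**The case against.** The best reply is that nothing here is an error. The site-only model is valid, it matches a randomisation stratified by site alone, and the sample size delivers its stated 90%. The protocol summarises its statistics and promises a detailed analysis plan, where covariates are often listed, and the wording about site does not forbid others. A single correctly specified score with no missing values also flatters the gain compared with several real covariates.

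Much of this stands. It makes the point one of efficiency, and the unseen plan may already deal with it. It does not remove the point, because section 10.2 names the primary model and its adjustment variable, so adding covariates changes a stated method. The objection that site might absorb the gain is met by the simulation with site in both models.

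Three stronger readings are tempting and are not supported.

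- A reader might infer that power would rise to 93-95%. That needs R2 of about 0.10-0.20, and the protocol gives no figure for how well these variables predict death. For the same reason they can be called likely predictors, but not strong ones.
- A reader might infer that the covariates will be available for every patient. Collection is planned for all, but section 6 lets data that cannot be obtained be registered as missing.
- A reader might add SAPS-III as an obvious severity score. Its present window makes that unsafe without a change to how it is collected.

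**Conclusion.** The point holds as a recommendation to improve efficiency. The primary analysis as written is unbiased and has its planned power, but it leaves available precision unused. At 1808 patients, adjustment would raise power from 90.0% to between 91.4% (R2 0.05) and 96.3% (R2 0.25). The direction is well founded, while the size depends on that assumed R2 and on covariates that are nearly complete. At the low end the gain is only 1.4 points. Even so, the change costs little.

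**What to change.** Before unblinding, pre-specify the primary model and the complications model as a site random intercept plus a short list of covariates fixed at or before randomisation: age, Clinical Frailty Scale, Charlson index, screening lactate and noradrenaline dose in the 6 h before enrolment.

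- Include SAPS-III only if it is restricted to pre-randomisation values. That may mean changing the data-collection instruction; otherwise leave it out.
- State a simple imputation rule for missing baseline values, so that no randomised patient drops out of the model for want of a covariate.
- Report the marginal risk ratio and risk difference by the G-computation already named in section 10.2.
- Keep the site-only model as a sensitivity analysis.

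Without SAPS-III, the cost is wording in the analysis plan and a matching line in section 10.2, with no new patients or data items. There are two small downsides: the list must be settled in advance and then left alone, and the odds ratio from the model becomes conditional on the covariates, so the marginal risk ratio should be the headline estimate.

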#### 4.4 Exit from the trial

A participant or his/her surrogate is free to withdraw from the trial at any time. A participant will exit the trial if the participant withdraws her/his consent. The participant making the withdrawal of consent will be asked for permission to use the data acquired up to that time point and if data for the primary endpoint can be collected. If permission is obtained, the participant will be included in the final analyses. If the participant declines, all data with the exception of initials, sex and date of withdrawal will be destroyed. If the trial intervention is discontinued by the treating physician because of adverse events, if the participant is withdrawn from active care and/or the focus of care is changed to palliation, or any other reason, this does not constitute withdrawal from the trial and the participant will not exit the trial (data collection will continue). A participant transferred to a non-REDUSE ICU will not exit the trial. All participants randomized in this trial will be analysed on an intention-to-treat basis.

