#### 10.1.2 Secondary outcomes

Based on a minimally important relative risk reduction of 20% and a rate of complications in the control group of 30%, the sample size yields a power of 99% for the complications outcome (Meyhoff 2022).

Based on a minimally important difference of 2 days, and the data collected in the REDUSE feasibility trial (Lindén 2024), we used simulations to ascertain the power using Van Elteren as the primary analysis. Using 1,000 iterations, we found a power of 80% mechanical ventilation-free days outcome.

Based on a minimal important difference of 1.5, a standard deviation of 2.8, (Hodgson 2022) the sample size yields a power of 100% for the MOCA-BLIND score outcome.

Based on a minimal important difference of 5 points, a standard deviation of 20 points, the sample size yields a power of 99% for the EQ-VAS score outcome (Contrin 2013, Granja 2004, Hammond 2020).

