## 10.3 Missing data

Missing data will be handled according to the recommendation by Jakobsen et al. 2017. We anticipate that the proportion of missing values on primary and secondary outcomes other than health-related quality of life and cognitive function will be less than 5%. For health-related quality of life and cognitive function we expect missing data to be less than 15%.

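### MoCA-BLIND and EQ-VAS are planned as an intention-to-treat linear comparison, but the planning figures fit only survivors; a mortality benefit can then tilt the test towards apparent harm, and the EQ-VAS power is overstated

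*Protocol*

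**What the plan says.** Section 10.2 fixes the model for both 6-month scores: "Secondary continuous outcomes (MoCA-BLIND and EQ-VAS) will be analysed using mixed effects linear regression with site as a random intercept". The same section calls the analysis intention-to-treat, and section 4.4 says "All participants randomized in this trial will be analysed on an intention-to-treat basis". The introduction to section 10 defines that population as every randomised patient who consented to use of their data, which includes those who die.

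Section 10.1.1 plans for an "expected 90-day mortality of 45 % in the control group" and is sized "To detect an absolute reduction in mortality of 7.5" percentage points, which implies 37.5% in the intervention arm.

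On missing data, section 10.3 says "For health-related quality of life and cognitive function we expect missing data to be less than 15"%. Section 10.1.2 derives the EQ-VAS power of 99% as follows: "Based on a minimal important difference of 5 points, a standard deviation of 20 points". For MoCA-BLIND it uses a difference of 1.5 and an SD of 2.8, and quotes a power of 100%.

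The protocol gives a dead patient no value on either scale. In contrast, the GOSE scale in Appendix A has a category for death, and section 3.4 describes the ventilation outcome as days alive and free of ventilation.

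**The concern.** A patient who dies before 6 months has no MoCA-BLIND or EQ-VAS score, and whether a patient survives may depend on the allocated arm. A comparison of survivors is therefore not protected by randomisation. If the intervention saves lives, its survivors include patients with no counterpart among control survivors. If those patients are in worse condition, they lower the intervention mean although nobody's score has been changed. By the same logic, a strategy that increased deaths among frail patients would make its survivors look better.

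The direction matters here. Section 3.4 gives an earlier association between fluid restriction and impaired cognition as background for the cognitive outcome, so the artefact of a life-saving strategy points the same way as the harm being looked for. Section 10.2 applies a threshold of 0.05 to these outcomes, and section 11 places them in the main publication.

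**Working it through.** **Check of the mortality inputs.** For 45% against 37.5%, two-sided 5%, 90% power, no continuity correction:

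n per arm = [1.960·√(2·0.4125·0.5875) + 1.2816·√(0.45·0.55 + 0.375·0.625)]² / 0.075² = (1.3645 + 0.8896)² / 0.005625 ≈ 903.3, rounded up to 904, so 1808 in total. This matches "a power of 90% the required sample size is 1808". Planned enrolment is 1850 ("we will include a total of 1850 patients"), or 925 per arm.

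**Do the planning figures include deaths?**
- Expected missingness below 15% is far under the 37.5-45% expected to die, so deaths are not counted as missing.
- If deaths scored 0 on EQ-VAS, with survivor SD 20 and survivor mean m, the control-arm SD would be √[0.55(400 + m²) − (0.55m)²]. That is 33.3 at m = 60 and 37.9 at m = 70 (both means assumed). Even with no spread among survivors, an SD of 20 would require a survivor mean of at most 20/√(0.55·0.45) = 40.2. The same bound for MoCA-BLIND is 2.8/√(0.55·0.45) = 5.6 points.
- All three sources cited for the EQ-VAS inputs have titles that refer to survivors.

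**Share of additional survivors.** (0.45 − 0.375)/(1 − 0.375) = 0.12 of intervention-arm survivors.

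**Assessed survivors at 15% missing.** Control 925·0.55·0.85 = 432; intervention 925·0.625·0.85 = 491. Mortality at day 90 stands in for mortality at 6 months, for which no figure is given.

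**Rejection with no effect on any score.** Let the additional survivors score D SDs below the others (D is an assumption). In SD units the expected difference is 0.12·D. The intervention-arm variance is 1 + 0.12·0.88·D², and SE = √[1/432.4 + (1 + 0.1056·D²)/491.4]. For D = 0.5, SE = √(0.002313 + 0.002089) = 0.0663 and z = 0.06/0.0663 = 0.90. The rejection probability is Φ(0.90 − 1.96) + Φ(−0.90 − 1.96) = 14.8%.

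| Gap D (SD) | EQ-VAS bias (0.12·D·20) | MoCA bias (0.12·D·2.8) | z | Rejects, two-sided | Of which towards harm |
|---|---|---|---|---|---|
| 0 | 0 | 0 | 0 | 5.0% | 2.5% |
| 0.25 | 0.6 | 0.08 | 0.45 | 7.4% | 6.6% |
| 0.5 | 1.2 | 0.17 | 0.90 | 14.8% | 14.6% |
| 0.75 | 1.8 | 0.25 | 1.35 | 27.0% | 27.0% |
| 1.0 | 2.4 | 0.34 | 1.78 | 42.7% | 42.7% |

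A simulation with a site-adjusted linear model (30 sites assumed, 4000 runs) gives 5.2%, 14.3% and 39.1% at D = 0, 0.5 and 1.

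**Bias against the minimal important differences.** To reach them by bias alone, D would have to be 5/0.12 = 41.7 EQ-VAS points or 1.5/0.12 = 12.5 MoCA points.

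**EQ-VAS power (5 points, SD 20).**
- All 1850 randomised: SE = 20·√(2/925) = 0.930, power 99.97%.
- All expected survivors of 1850: power 98.4%.
- 85% of expected survivors: SE = 20·√(1/432.4 + 1/491.4) = 1.319, 5/1.319 = 3.79, power Φ(3.79 − 1.96) = 96.6%. With 1808 randomised it is 96.3%.

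MoCA-BLIND power stays at about 100% in every case (1.5/(2.8·0.0659) = 8.1 standard errors with 85% of survivors).

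**The case against.** The strongest objection is that section 10 is a summary. It promises a detailed statistical analysis plan before the last randomisation, and that plan may say how deaths enter these scores. The absence of such a rule from the protocol is not itself an error. What stands is that the protocol already fixes the model, the SDs and the powers, and labels as intention-to-treat a set of figures that describe survivors.

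A reader might infer that the linear model can only compare survivors. The documents do not say so: the same model could be run with a value assigned to death. The survivor reading is an inference. The missingness figure alone does not settle it, because deaths would not be missing under a scored analysis either. The SDs and their sources carry the inference.

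A reader might also infer that the trial is likely to report a false cognitive harm. That does not follow. The gap D is not in the documents; at zero gap the error rate is 5%, and at 0.5 SD about 85% of trials do not reject. The bias is well below the protocol's minimal important differences. Section 10.2 bases its primary conclusions on mortality and calls secondary results hypothesis generating.

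Finally, a reader might conclude that a rank test with deaths placed lowest should replace the linear model. That would serve the stated purpose worse. In a simulation with the planned mortality difference (unstratified Wilcoxon, 925 per arm, 85% of survivors assessed, additional survivors scoring like the rest):
- with no effect on any score, the rank test rejects towards benefit in 82% of trials;
- under a true 5-point EQ-VAS harm it detects harm in 0% and rejects towards benefit in 25%, while the survivor model detects the harm in 96%;
- under a true 1.5-point MoCA harm it detects harm in about 5-6%, against about 100% for the survivor model.

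This part of the objection stands in full, so the rank test belongs in a supplementary role.

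**Conclusion.** The point holds in a limited form. The plan for the two 6-month scores is, on its own figures, a comparison of survivors under an intention-to-treat label. Under the planned mortality effect, 12% of intervention-arm survivors have no counterpart among control survivors, and the nominal 5% test rejects in about 7%, 15% or 43% of trials at gaps of 0.25, 0.5 or 1 SD with no effect on any patient. This assumes that the 90-day mortality difference carries to 6 months, that the intervention causes no deaths, that 15% of survivors are not assessed, and that the additional survivors score worse by the stated gap. The artefact can reach P < 0.05 but is unlikely to reach a minimal important difference, and the conclusion on mortality is unaffected.

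The EQ-VAS power does not depend on the gap: at the protocol's own 15% missing it is about 96-97% in assessed survivors, not 99%. The trial remains well powered for this outcome, so this is a correction of the figure and not a call for more patients.

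**What to change.** 1. In section 10.2, keep the mixed linear model, state that it compares survivors, and adjust it for baseline predictors of death and score that Appendix A already collects: age, Clinical Frailty Scale, Charlson index and SAPS-III. This reduces the survivor bias but does not remove it. In one simulated setting, adjustment lowered false rejection from 21% to 14%; the gain depends on how well the covariates predict both death and score.
2. Add, as a supplementary and not the lead analysis, a site-stratified van Elteren test with deaths ranked lowest, read beside mortality and the survivor means. Its downside should be stated: it mostly reflects mortality and can mask a true harm to cognition or quality of life when mortality improves.
3. State that a survivor difference will not by itself be read as an effect on cognition or quality of life when mortality differs in the direction that could explain it.
4. In section 10.1.2, state that the SDs of 20 and 2.8 refer to survivors, and give the EQ-VAS power as about 96-97% (expected survivors of 1850, 15% missing). The MoCA-BLIND figure stays at about 100%.

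The cost is wording in two sections, four covariates in the model and one further analysis per outcome. No new data and no more patients are needed.
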